## Abstract

**Background:**

High dose unilobar radioembolization (also termed ‘radiation lobectomy’)—the transarterial unilobar infusion of radioactive microspheres as a means of controlling tumour growth while concomitantly inducing future liver remnant hypertrophy—has recently gained interest as induction strategy for surgical resection. Prospective studies on the safety and efficacy of the unilobar radioembolization-surgery treatment algorithm are lacking. The RALLY study aims to assess the safety and toxicity profile of holmium-166 unilobar radioembolization in patients with hepatocellular carcinoma ineligible for surgery due to insufficiency of the future liver remnant.

**Methods:**

The RALLY study is a multicenter, interventional, non-randomized, open-label, non-comparative safety study. Patients with hepatocellular carcinoma who are considered ineligible for surgery due to insufficiency of the future liver remnant (< 2.7%/min/m^2^ on hepatobiliary iminodiacetic acid scan will be included. A classical 3 + 3 dose escalation model will be used, enrolling three to six patients in each cohort. The primary objective is to determine the maximum tolerated treated non-tumourous liver-absorbed dose (cohorts of 50, 60, 70 and 80 Gy). Secondary objectives are to evaluate dose–response relationships, to establish the safety and feasibility of surgical resection following unilobar radioembolization, to assess quality of life, and to generate a biobank.

**Discussion:**

This will be the first clinical study to assess the unilobar radioembolization-surgery treatment algorithm and may serve as a stepping stone towards its implementation in routine clinical practice.

**Trial registration:**

Netherlands Trial Register NL8902, registered on 2020–09-15.

## Background

Hepatocellular carcinoma (HCC) is a frequent cause of cancer death with limited treatment options [1]. Although surgical resection is the most important curative treatment for patients with HCC, it is feasible in only a minority of cases, even when the disease is confined to the liver [1, 2]. Resection is frequently precluded due to insufficiency of the ‘future liver remnant’ (FLR), the part that is to remain after resection. To increase the safety of surgical resection, a common strategy is to preoperatively embolize the ipsilateral portal vein [3]. Contralateral shunting of portal blood induces hypertrophy of the FLR that allows safer partial hepatectomy [3]. However, hypertrophy induction may fail especially in patients with low FLR function [4]. In addition, portal vein embolization does not confer tumour control, which is especially disadvantageous in patients with HCC given the lack of effective neoadjuvant therapy. A number of studies have demonstrated accelerated progression of existing tumours after portal vein embolization [5–10]. Therefore, techniques to induce FLR growth that simultaneously confer ipsilateral tumour control may benefit patients.

Radioembolization, an intrahepatic radiation treatment for liver tumours, is a promising candidate technique. Radioembolization involves intra-arterial infusion of yttrium-90 (^90^Y) (SIR-Spheres®, Sirtex or TheraSphere™, Boston Scientific) or holmium-166 (^166^Ho) (QuiremSpheres®, Quirem Medical) loaded microspheres to the liver. Patients who received unilobar treatment (i.e., to the right or left hepatic artery) were found to have marked atrophy of the treated lobe and hypertrophy of the non-irradiated lobe [11]. This response to radioembolization has therefore also been coined ‘radiation lobectomy’, but we will use the term ‘unilobar radioembolization’ throughout this paper.

It has been demonstrated that unilobar radioembolization (i) induces slower, but eventually similar or even more pronounced FLR hypertrophy than portal vein embolization; (ii) is safe; and (iii) allows for subsequent resection [11–20]. Resection specimens obtained after radioembolization reveal significant necrosis with complete obliteration of the tumour in 30% of resected specimens [13]. As such, unilobar radioembolization may increase the likelihood of tumour-free resection margins, especially in the case of tumours close to major bilio-vascular structures. Unilobar radioembolization can be used as a ‘test-of-time’: if new lesions are discovered during the FLR hypertrophy phase—for example due to the outgrowth of already existing micro metastases—this prevents unnecessary surgery. Although all phases of the unilobar radioembolization-surgery treatment modality have been studied retrospectively, prospective studies are still lacking.

Currently available microspheres include ^90^Y and ^166^Ho-based microspheres. The characteristics of the radionuclide ^90^Y limit its use as a scout dose to simulate treatment, as it cannot be accurately visualized at low activity. Therefore, the safety scout dose must consist of surrogate particles (namely Technetium (99mTc) albumin aggregated (^99m^Tc-MAA) that differ substantially from ^90^Y microspheres in size, number and shape, lowering their validity as a predictor for microsphere distribution [21]. The newly developed ^166^Ho microspheres have distinctive advantages over the existing ^90^Y microspheres in terms of quantitative nuclear imaging. ^166^Ho can be visualised on both SPECT/CT and MRI, which improves estimation of lung shunting, intrahepatic distribution, and assessment of therapeutic activity [22, 23]. As the treated non-tumourous liver-absorbed dose seems to be of importance in driving FLR response, accurate dosimetry is assumed to be a prerequisite for optimal safety and efficacy in the unilobar radioembolization setting [18].

We previously showed that ^166^Ho radioembolization, with a projected average absorbed dose of up to 60 Gy to the whole liver, was safe for patients with liver metastases [24], and hepatocellular carcinoma [25]. However, the optimal safety dose to the non-tumourous liver tissue of the treated lobe for patients designated for unilobar radioembolization has not been established. Such data is especially important for patients with HCC, who often have vulnerable livers due to chronic liver disease [1, 2]. In this dose escalation study, the safety and efficacy of ^166^Ho unilobar radioembolization will be investigated in patients with hepatocellular carcinoma that are irresectable due to insufficiency of the FLR.

## Methods/design

### Aims and outcomes

The primary objective of this study is to establish the maximum tolerated non-tumourous liver-absorbed dose of ^166^Ho microspheres in patients with HCC who receive unilobar radioembolization as a bridge to resection. The maximum tolerated dose is assessed in terms of the rate of unacceptable dose-limiting toxicities (see paragraph on Design). All grade 3 or higher toxicities (according to the CTCAE version 5.0 criteria) that are possibly, probably or definitively related to unilobar radioembolization are considered a dose-limiting toxicity. Exceptions to this are expected adverse events: grade 3 or higher lymphopenia and liver enzymes (AST/SGOT, ALT/SGPT, GGT, ALP), as well as post-embolization syndrome. Toxicities after unilobar radioembolization will be recorded at 6 weeks, 3, 4.5, 6 and 9 months, or up to three months after surgery. Administration technique related adverse events will not be regarded as dose-limiting toxicity.

Secondary aims include establishing a dose–response relationship between (i) the perfused/treated normal liver-absorbed dose and the FLR response and (ii) the tumour-absorbed dose and the tumour response, to map the safety and feasibility of surgical resection of converted patients, and to assess quality of life during the study procedures. FLR response will be quantified using MRI (volume of the FLR) and hepatobiliary iminodiacetic acid (HIDA) scan (function of the FLR). Tumour response will be assessed using the mRECIST criteria [26]. Dose–response relationships will be measured at baseline and at every post-unilobar radioembolization follow-up. The safety and feasibility of surgical resection will be monitored through the Clavien-Dindo grading system during the post-operative stay and at the follow-up visit three months after surgery [27]. Quality of life of patients will be assessed at every visit through questionnaires in the patient’s native language. EORTC QLQ C30, EORTC QLQ HCC and BPI-SF questionnaires and manual will be used for assessment and analysis respectively [28–30].

As a last secondary aim, a biobank will be generated of resected liver specimens and blood samples for future analyses of therapy surviving cancer cells.

### Design

The RALLY study is a multicenter, interventional, non-randomized, open-label and non-comparative study. A classical 3 + 3 dose escalation model with four cohorts will be used, enrolling three patients in each cohort (Fig. 1). The first cohort of patients will receive an amount of radioactivity corresponding to a projected average absorbed dose of 50 Gy to the treated non-tumourous liver parenchyma. The non-tumourous liver-absorbed dose is estimated by means of a ^166^Ho-microsphere scout dose [31]. If none of the patients in the first cohort experience a dose-limiting toxicity, the non-tumourous liver dose will be escalated to 60 Gy in a cohort of three new patients. If one patient in a cohort experiences a dose-limiting toxicity, the cohort is increased to six patients. If two or more patients in a cohort develop a dose-limiting toxicity, the maximal tolerable dose is reached and further dose escalation will be ceased. Escalation will cease if no dose-limiting toxicity is found in the 80 Gy cohort. As such, a maximum of four cohorts will be recruited. The last cohort will always consist of six patients to confirm safety.

**Fig. 1 Fig1:**
[figure not shown]
Dose escalation example. Green circles represent patients that did not experience a dose-limiting toxicity at a given dose. Red circles represent patients that did experience a dose-limiting toxicity. The y-axis represents the dose to the non-tumourous liver tissue. In this example, two patients in the 80 Gy cohort experienced a dose-limiting toxicity, meaning the maximal tolerable dose is found and set to 70 Gy (with 18 patients included). The escalation will halt if no maximal tolerable dose is found after 80 Gy. Note that the last safe cohort will always include six patients

Inclusion of patients in the next cohort will be performed if (i) all patients have received the treatment dose at least six weeks prior and (ii) the Data and Safety Monitoring Board (see Monitoring) has scrutinized the toxicity data and gave permission to proceed.

### Study population

All patients with HCC in whom upfront surgery is precluded because of insufficient function of the FLR will be included. These are patients with HCC and preserved liver function who have nodules larger than 2 segments, and are not suitable candidates for radiofrequency ablation or liver transplantation (for example in the case of cirrhosis). Insufficient FLR function is defined as a HIDA scan clearance of 1.5—2.7%/min/m^2^ [32]. The complete list of inclusion and exclusion criteria are detailed in Supplementary Table S1. Patients will be identified in the respective tumour boards and subsequently discussed in an expert panel prior to inclusion. Informed consent will be taken by trained personnel with a ‘good clinical practice’ certification who have no treatment relationship with the patient. Patients will be included in the University Medical Center Utrecht, Amsterdam University Medical Center, Erasmus Medical Center (all in the Netherlands) and Regina Elena National Cancer Institute (Italy).

### Intervention, study procedures and timeline

The medical device under investigation contains the radionuclide holmium-166, marketed as QuiremSpheres® and QuiremScout®. In contrast to ^90^Y, ^166^Ho emits both gamma-radiation (81 keV) and high-energy (1.81 MeV) beta-particles. The beta-particles are responsible for the therapeutic effect of the device; the gamma-radiation may be used for nuclear imaging purposes (i.e., SPECT/CT). Patients will receive treatment to just one liver lobe (i.e., the left or right branch of the hepatic artery, ± the segment IV artery).

The study exists of a screening visit, a scout dose, the actual therapeutic dose, the post-unilobar radioembolization follow-up visits, the surgical resection (if patients can proceed to surgery) and the post-surgery follow-up visit. The participant’s timeline is summarized in Fig. 2. Table 1 details the study procedures per visit.

**Fig. 2 Fig2:**
[figure not shown]
Study flowchart. Eligibility is assessed during the screening visit (patient and tumor characteristics) as well as the scout dose (lung shunting, extrahepatic depositions, etc.). Patients will be considered included once they received the actual treatment dose. The post-treatment follow-up visits serve to map toxicities, as well as to evaluate eligibility for resection. *The exact interval will be at 1.5, 3, 4.5, 6 and 9 months. The last follow-up will be at 9 months following treatment (if not converted) or 3 months after hepatectomy

**Table 1 Tab1:** Study procedures

Procedures	Screen	Scout	Treatment	SPECT/CT	Follow-up^a^	S	Post-S visit^b^
Informed consent	E						
In-/exclusion	E	E					
Demographic data	X						
Physical exam, vital signs and clinical performance status (ECOG)	X	E	X		X	X	X
EORTC QLQ C30, HCC 18, BPI-SF	E	E	E		E	E	E
MRI / CT liver	X				X^c^	X^c^	X^c^
CT thorax	X						
HBS	X				X		
Angiography		E	E^d^				
Scout dose		E					
Therapeutic dose			E				
SPECT/CT + contrast CT		E		E^e^			
Laboratory examination	X	E	X		X	X	X
Monitoring of (S)AE’s + concomitant med		E	X		X	X	X
Pregnancy test		X					

E = extra activity in study context, X = standard care, W = week, M = month, S = Surgery

^a^Exact interval is at 1.5, 3, 4.5, 6 and 9 months. However, post-radioembolization follow up will be discontinued as soon as patients are eligible to undergo surgical resection. ^b^Three months following surgery. ^c^MRI is standard. CT is performed if MRI is contraindicated. ^d^Venogram when standard therapy (PVE) is performed. ^e^Three to four days after the therapeutic treatment, at separate visit in outpatient clinic

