### Post-treatment follow-up

After treatment, patients will be tentatively scheduled for follow-up visits after 1.5, 3, 4.5, 6 and 9 months. The main goal of these follow-up visits is to evaluate the eligibility of the patient to proceed to surgical resection and to map the toxicity and response following ^166^Ho-radioembolization. The study participation for a patient will end if the patient is unable to undergo surgical resection within 9 months. During each visit, laboratory (Table 2) and clinical toxicities will be monitored. Tumour response is assessed using MRI (or CT if contra-indicated) with mRECIST [26]. FLR response is assessed using HIDA and MRI.

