### Hepatectomy and post-surgery follow-up

If tumour burden, performance status and FLR (> 2.7%/min/m^2^) allows for resection, the patient will be operated on as soon as possible. Eligibility for resection will be discussed in a multidisciplinary tumour board. The patient undergoes general anesthesia and the abdomen will be explored to rule out extrahepatic disease. The extent of the hepatectomy will be determined intraoperatively with the aim of achieving R0 resection. Directly following resection, surgical specimens of both tumour- and non-tumour tissue will be processed for routine histological evaluation as well as inclusion in the RALLY biobank (see heading ‘Biobank’). After resection, patients will receive a last follow-up visit three months after resection during which toxicities, surgical complications (using Clavien-Dindo) and tumour burden will be assessed [27].

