### Statistics and data management

#### Statistical analysis

Descriptive statistics (n, mean, standard deviation, 95-CI, median, minimum and maximum) will be calculated for each quantitative variable; frequency counts by category will be made for each qualitative variable. Two sets of study data will be evaluated: the primary endpoint will be evaluated in the Full Analysis Set. The Full Analysis Set is defined as the set of data generated from the included patients who received at least the treatment dose. The secondary endpoints will be evaluated in both Full Analysis Set and Per Protocol Set. The Per Protocol Set is defined as the set of data generated from the included patients who complied with the protocol. A linear mixed effects regression model will be used to evaluate the relationship between absorbed dose- and studied effect. An analysis of variance method with a Chi-square test will be used to compare nested models and generate p-values for the fixed effects. The explained variance by the model, with and without random intercept, will be assessed with R^2^ for mixed effects models.

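### Scheduled toxicity visits end at eligibility for resection, so a patient declared eligible but never resected has no scheduled late toxicity visit

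*Protocol article*

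**What the plan says.** Four places in the protocol article fix how long toxicity is recorded.

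- **Aims and outcomes** sets the window for the primary endpoint: "Toxicities after unilobar radioembolization will be recorded at 6 weeks, 3, 4.5, 6 and 9 months, or up to three months after surgery".
- **Fig. 2 legend** sets the end of follow-up: "The last follow-up will be at 9 months following treatment (if not converted) or 3 months after hepatectomy".
- **Table 1, footnote a** lists the same visit times and then cuts them short: "However, post-radioembolization follow up will be discontinued as soon as patients are eligible to undergo surgical resection".
- **Post-treatment follow-up** sets the end of participation: "The study participation for a patient will end if the patient is unable to undergo surgical resection within 9 months".

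Hepatectomy and post-surgery follow-up says of a patient who meets the resection criteria that "the patient will be operated on as soon as possible", with no fixed interval. It also says that at operation "the abdomen will be explored to rule out extrahepatic disease". Statistical analysis evaluates the primary endpoint in the Full Analysis Set, defined as "the set of data generated from the included patients who received at least the treatment dose".

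**The concern.** Eligibility and hepatectomy are different events, and footnote a attaches the end of the visits to the earlier one. The next scheduled assessments are the surgery visit and the visit three months after surgery. If the hepatectomy does not happen, the post-surgery visit does not occur either, and nothing says that the stopped visits start again.

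The article itself foresees such patients. Exploration is meant to look for extrahepatic disease, resection depends on tumour burden and performance status, and the Background values the waiting period because new lesions may appear. Refusal is a further route.

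The primary objective is a maximum tolerated dose from a 3 + 3 rule. One DLT among three patients expands the cohort, and two or more in a cohort stop escalation. With so few patients, a single missed late DLT can change a cohort's count. These patients also keep the irradiated lobe, so their late toxicity is relevant to the question.

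**Working it through.** **1. The plan's own figures.** The article gives no number for this point. Its sample sizes reproduce, (3 + 3) × 4 = 24 and 3 × 4 + 3 = 15, and are not affected.

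**2. The statements side by side, for a patient eligible but never resected.**

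| Place | End of toxicity recording |
|---|---|
| Aims and outcomes | 9 months, since there is no surgery to count from |
| Table 1 footnote a | the visit at which eligibility is declared |
| Fig. 2 legend | 9 months only if the patient counts as not converted |
| Post-treatment follow-up | in the study until 9 months; no word on resuming visits |

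The word converted is not defined. Aims and outcomes speaks of resecting converted patients and the Discussion of converting patients to resectability, which suggests that it means becoming resectable. The Fig. 2 legend contrasts it with hepatectomy, which suggests that it means being resected. On the first reading the 9-month branch is lost. On the second it applies, but footnote a has already stopped the visits.

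**3. How much recording is lost.** Visits are at 1.5, 3, 4.5, 6 and 9 months. Time lost is 9 minus the time of eligibility.

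| Eligibility declared at | Visits not held | Time without a follow-up visit |
|---|---|---|
| 1.5 months | 4 | 9 − 1.5 = 7.5 months |
| 3 months | 3 | 9 − 3 = 6 months |
| 4.5 months | 2 | 9 − 4.5 = 4.5 months |
| 6 months | 1 | 9 − 6 = 3 months |

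The Discussion expects sufficient response of the future liver remnant at three to five months, so the middle rows are the likeliest. If exploration takes place, the surgery visit adds one assessment, because Table 1 schedules laboratory tests and adverse event monitoring there.

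**4. What this could do to the count.** The documents give no DLT rate, no share of patients eligible but never resected, and no timing of DLTs, so an effect can only be illustrated. Let p be the true DLT rate, e the share eligible but never resected, and m the share of their DLTs that fall after visits stop and go unrecorded. Suppose further that unrecorded is read as absent and that the full count is available at the decision. Then

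- observed rate = p × (1 − e × m)
- P(cohort passes) = (1 − p)³ + 3p(1 − p)⁵

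Example with p = 0.33, e = 0.2, m = 0.5: the observed rate is 0.33 × 0.90 = 0.297. The pass probability is 0.67³ + 3 × 0.33 × 0.67⁵ = 0.434 at the true rate and 0.703³ + 3 × 0.297 × 0.703⁵ = 0.500 at the observed rate.

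| p (assumed) | e | m | Observed rate | P(pass), true | P(pass), observed |
|---|---|---|---|---|---|
| 0.20 | 0.1 | 0.25 | 0.195 | 0.709 | 0.719 |
| 0.20 | 0.2 | 0.5 | 0.180 | 0.709 | 0.752 |
| 0.20 | 0.3 | 1 | 0.140 | 0.709 | 0.834 |
| 0.33 | 0.1 | 0.25 | 0.322 | 0.434 | 0.451 |
| 0.33 | 0.2 | 0.5 | 0.297 | 0.434 | 0.500 |
| 0.33 | 0.3 | 1 | 0.231 | 0.434 | 0.641 |

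If e or m is zero, there is no effect. All values of p, e and m are assumptions. The table shows direction and range and is not an estimate for this trial.

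**The case against.** The strongest reply is that this is loose wording in a condensed article. Not converted can be read as no hepatectomy, and Post-treatment follow-up ties the end of participation to resection rather than eligibility. A sensible site would then keep seeing the patient to 9 months. Surgery is meant to follow quickly, so the interval after eligibility should be short for most patients. This stands in part: it shows that the intention may be sound. It does not remove footnote a, which is an explicit rule, and no passage restarts the visits it stops.

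Two stronger readings are tempting and are not supported.

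- A reader might infer that the Full Analysis Set counts these patients as DLT-free and so biases the DLT rate downward. The definition says only who is in the set. It has no rule for incomplete follow-up, and such a rule may stand in the full protocol or statistical analysis plan, which are not shown.
- A reader might treat such a patient as wholly unobserved and derive a large rise in the cohort's chance of passing. That does not describe these patients. Eligibility is judged at visits that also record toxicity, the first at six weeks, so 6-week data should exist. The step to the next cohort also needs more than six weeks since dosing: under Design, the data and safety monitoring board must have reviewed the toxicity data and given permission.

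**Conclusion.** The concern holds in a limited form. Table 1 footnote a conflicts with the toxicity window under Aims and outcomes, and Post-treatment follow-up does not resolve the conflict. As written, a patient declared eligible but never resected has no scheduled toxicity visit after eligibility, other than a surgery visit if exploration takes place. The loss is one to four scheduled visits, all of them late.

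Any effect on the DLT count is conditional. It requires that such patients occur, that some have a DLT after visits stop which no other route captures, and that unrecorded is read as absent. If all three hold, the count could be too low, by an amount that the documents do not allow one to compute. Toxicity at six weeks, the minimum interval before the next cohort, is not in question.

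**What to change.** Reconcile Aims and outcomes, the Fig. 2 legend with Table 1 footnote a, and Post-treatment follow-up. In footnote a, tie the end of the existing toxicity visits to completed hepatectomy rather than to eligibility, so that treated patients without a hepatectomy stay on the existing visit schedule to 9 months. Define converted, or replace it in the legend by whether a hepatectomy was completed. Every treated patient then has a defined end of DLT recording.

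The cost is protocol wording and a few existing visits for a few patients.

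A DLT-evaluable set that requires completed recording is not recommended as part of this change. Recording runs to 9 months or three months after surgery, so no DLT-free patient could be counted at the six-week step to the next cohort, and the escalation timing would have to be rewritten.
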